### Statistical analyses

Statistical analyses will be carried out STATA Version 17 (StataCORP LLC, Texas, USA).

We will exclude participants with single-item missing data relevant to the analysis and will not perform imputations. An intention-to-treat analysis will be employed to maintain the integrity of our results. A per-protocol analysis will also be performed to complement the primary intention-to-treat analysis. While the intention-to-treat analysis preserves the advantages of randomisation and reflects real-world implementation challenges, the per-protocol analysis may help assess the true effect of receiving the intervention as intended. Given the negligible planning costs and absence of adverse effects, the intervention may still be considered clinically relevant even if statistical significance is only observed in the per-protocol population.

Characteristics will be reported with numbers, percentages and means with standard deviations or medians with interquartile range, as appropriate. Differences will be calculated using appropriate tests. Appropriate regression analyses will be conducted according to advice from a research statistician. Threshold for significance will be *P* < 0.05.

Readmission and mortality will be calculated and compared as relative risks. We will conduct an interim analysis after 1 year to adjust the time length of the study and to assure that one group does not have a significantly higher mortality rate or readmission rate than the other, which are the stopping criteria. The outcomes examined in the interim analysis will be 30-day mortality and 30-day readmission rate. The interim analysis will be conducted on data masked by a third party to ensure blinding, and the data will not be unblinded unless there is a significant difference in mortality, which is the only stopping criteria. The interim analysis will be conducted after 13 months have passed, i.e. January 2024.

The financial costs analyses will be conducted under supervision of a health economist, [name]. We will analyse our data including time spent by the health professionals and estimate intervention cost per participant, which will be compared to an estimated daily cost of admission and the estimated avoided readmission days.

Qualitative analysis will be conducted to assess user perspectives. This will be conducted as a separate parallel study by [name] [name].

We will use the EQUATOR Network guidelines, e.g. the CONSORT 2010 statement, when presenting the results of our study.

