### Data collection

Data will be collected at several points. The data will all be saved and stored in a secure database (REDCap). All personnel involved will be trained data collection.

Before the participant is invited to join the study, data is gathered on eligibility (i.e. diagnosed moderate to severe dementia, residence location to identify citizens of Odense Municipality, and type, use of home care, terminal diseases and presence of delirium).

Before discharge, data is gathered from the participants’ electronic medical records regarding discharge diagnoses, LOS, medication, medical history and Barthel ADL score [39]. A Clinical Frailty Score [40] is assessed by a geriatric nurse.

All data collected during the follow-up visit is registered in our database, including the data gathered in the FS-III survey, vital status and POCT results. The vital parameters and POCT results will be used to understand their influence on the clinical decision making.

The data collected during the follow-up visit will be filled directly into pre-defined fields in REDCap and will help ensure that all the necessary data is collected.

All participants, controls and interventions will receive a questionnaire, which is a modified version of a previously validated questionnaire [41]. At the time of randomisation, both groups will be asked about their satisfaction with the treatment, care and hospitalisation in general, as well as if they feel safe being discharged. A follow-up questionnaire will be administered to both groups by telephone. Data will be transferred to REDCap manually. The questionnaires will be administered by project coordinators who are not involved in the clinical care of the patients.

Data on death and readmissions will be collected from electronic medical records for 1 year after the allocation date for each participant.

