### Analyses of primary and secondary outcomes

The primary outcome is 30-day acute readmission. We will use relative risks to compare the readmission rates in the two groups. Relative risk for other readmission time frames will also be calculated to improve comparisons with other studies.

Competing risk of death will be considered in our analyses, as it can skew the results. Partially due to this, days out of hospital will also be calculated as it is less affected by the competing risk of death than a binary readmission outcome.

We will also calculate the relative risks for 30-day mortality.

A proportional hazard model will be used to explain the time to readmission. This will be done using the Cox regression model. Moreover, median time to readmission will be estimated by the Kaplan–Meier method.

We will include relevant patient characteristics that are known risk factors in our statistical analyses, e.g. multimorbidity, polypharmacy and length of stay.

Throughout the analyses, we will adjust for participants that were already readmitted at the time of recruitment. Separate analyses will be done for patients that already received the intervention, as there may be a residual effect of the intervention.

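### In covariate-adjusted analyses, complete-case exclusion without imputation would drop randomised participants whose readmission status is known, at odds with the intention-to-treat claim

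*Protocol article*

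**What the plan says.** Four statements in the protocol article bear on this point.

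- **Missing data** (Statistical analyses): "We will exclude participants with single-item missing data relevant to the analysis and will not perform imputations".
- **Analysis principle** (same section, next sentence): "An intention-to-treat analysis will be employed to maintain the integrity of our results". The paragraph treats this as the primary analysis, with per-protocol as a complement.
- **Outcome source** (Data collection): "Data on death and readmissions will be collected from electronic medical records for 1 year after the allocation date for each participant".
- **Comparison and covariates** (Analyses of primary and secondary outcomes): "We will use relative risks to compare the readmission rates in the two groups". The same section adds "We will include relevant patient characteristics that are known risk factors in our statistical analyses, e.g. multimorbidity, polypharmacy and length of stay", and also "Throughout the analyses, we will adjust for participants that were already readmitted at the time of recruitment".

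The covariate list is open, and the article does not say which analyses the covariates enter. It mentions no sensitivity analysis for missing data.

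**The concern.** The advantage of intention-to-treat is that everyone randomised is compared in the arm to which they were allocated. A rule that deletes people because a baseline field is blank gives part of that up. Here the loss would be avoidable: readmission and death come from records and should be known for nearly every participant, so the deleted people would mostly be people whose outcome is available.

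A covariate placed in a model is plainly an item relevant to that analysis, so the rule reaches every adjusted model. With several covariates, small losses on each add up. At stake are the population that the adjusted estimates describe and their precision. This is not a detail left for an analysis plan to settle, because the article fixes the rule and expressly closes off imputation.

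**Working it through.** **1. Which analyses the rule reaches**

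| Analysis | Items it needs | Can the rule remove someone with a known outcome? |
|---|---|---|
| Unadjusted relative risk of 30-day readmission | Allocated arm; readmission status from records | No |
| Same, adjusted for readmitted status at recruitment | As above, plus a fact known at recruitment | Practically no |
| Models with multimorbidity, polypharmacy, length of stay and other risk factors | As above, plus each covariate | Yes, if any one covariate is blank |

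**2. Whether missingness could depend on arm**

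Table 1 schedules multimorbidity, polypharmacy and length of stay at discharge. Data collection takes medication, medical history and length of stay from hospital records before discharge. The Blinding section keeps allocation hidden until discharge. Planned weekend discharges are randomised on the Friday, so length of stay is completed after randomisation for them, but it is an administrative figure that should rarely be missing. No item collected at the home visit is named as a covariate in a comparison between arms.

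**3. The plan's own sample size**

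Inputs (Sample power and statistical power): p1 = 0.19; p2 = 0.19 × (1 − 0.28) = 0.1368; α = 0.05, taken as two-sided; power 0.80; 1:1 allocation.

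n per arm = [1.960 × √(2p̄(1−p̄)) + 0.842 × √(p1(1−p1) + p2(1−p2))]² / (p1−p2)², with p̄ = 0.1634

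= [1.960 × 0.5229 + 0.842 × 0.5215]² / 0.0532² ≈ 758.

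The article states 763, which agrees within 1%. Its recruitment target follows as 1526 × 1.2 = 1831.2, rounded up to 1832, or 916 per arm.

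**4. Power as a function of participants kept**

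Power = Φ{[(p1−p2) − 1.960 × √(2p̄(1−p̄)/n)] / √((p1(1−p1) + p2(1−p2))/n)}

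At n = 763 this gives 80.3%; at n = 916 it gives 86.9%.

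**5. Loss from blank covariates**

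The share kept is (1−m)^k for k covariates, each missing with probability m, independently. Both k and m are assumptions, since the article gives no rate. Three is the number of covariates it names as examples; five allows for the open list.

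| k | m | Share kept | n per arm, from 916 | Power |
|---|---|---|---|---|
| 3 | 3% | 0.97³ = 0.913 | 836 | 83.8% |
| 3 | 5% | 0.95³ = 0.857 | 785 | 81.4% |
| 5 | 3% | 0.97⁵ = 0.859 | 787 | 81.5% |
| 5 | 5% | 0.95⁵ = 0.774 | 709 | 77.4% |

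The table assumes no other loss. If the planned 20% dropout also occurred in full, 0.8 × 916 ≈ 733 per arm would remain (78.7% power), and the five-covariate cases would fall to 72.4% and 67.9%.

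The two-proportion formula stands in for the adjusted model here, so the figures show the size of the loss and are not a forecast.

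**The case against.** The strongest reply is about scope. The exclusion is confined to items relevant to the analysis in question, and the stated primary comparison is a relative risk that needs little more than arm and readmission status. A reader might infer that anyone with any blank field is removed from the primary result. The text does not support that: a missing questionnaire answer, nursing-assessment item or point-of-care result takes nobody out of the plain relative risk. This part of the reply stands.

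A reader might also infer bias between arms, because the intervention group has an additional data-collection contact. That would need an item from the visit to serve as a covariate in a comparison between arms, and none is named. The named covariates are recorded by discharge, so their missingness should not follow allocation. This also stands, and no bias figure is offered here.

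A third reply is that the paragraph sets intention-to-treat against per-protocol, that is, allocation against receipt, so complete-case handling is a tension with it and not a flat contradiction. That is fair as to wording. It does not remove the consequence that adjusted analyses would leave out randomised participants with known outcomes.

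Finally, the 20% dropout allowance may absorb the loss. It can in part, which is why the main figures start from 916 and not 763 per arm. An allowance for attrition is still no reason to discard observed outcomes, and hospital-record covariates may turn out nearly complete, in which case the loss is small.

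**Conclusion.** The point holds for the covariate-adjusted analyses. There the stated rule would delete randomised participants whose readmission and death are known from records, so those analyses would not include all randomised participants and would be less precise than the data allow.

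Under the assumed missingness, power of 86.9% falls to between 83.8% and 77.4% when nothing else is lost. The size rests on three assumptions: the number of covariates, the rate at which each is missing, and independence between them. Independence gives close to the largest loss for given rates. The direction of the effect does not depend on these figures; any blank covariate costs a known outcome.

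The document does not establish that the unadjusted primary relative risk is compromised, or that the treatment effect would be biased. The change is worth making because the better method is simple and needs no new data.

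**What to change.** In Statistical analyses, replace the blanket rule with three statements.

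1. The primary intention-to-treat relative risk includes all randomised participants, in their allocated arm, with record-based 30-day readmission status, whatever else is missing.
2. In adjusted models, missing baseline covariates are filled in by a simple method that ignores arm (overall mean or mode, or a missing indicator). This is acceptable because covariates fixed before allocation is known are independent of arm by randomisation.
3. Complete-case exclusion is limited to outcomes that are truly unobserved, such as unanswered questionnaires. A complete-case version of the adjusted models is reported as a sensitivity analysis.

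The cost is a few sentences and minor extra programming. No new data are needed.

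The change should be made before the blinded data are analysed, together with a fixed list of the covariates that enter each model.

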### Setting and study population

The study will take place at the Department of Geriatrics Odense University Hospital Region of Southern Denmark (G-OUH) and in the Odense Municipality, Denmark.

Odense Municipality is by population the largest municipality in the Region of Southern Denmark and the 4th largest municipality in Denmark [21]. The population (2022) is approximately 206,000 [21], of which approximately 36,000 are 65 + years of age [21]. Odense Municipality has 14,000 employees [22], including 3500 employees caring for frail older adults and disabled persons [23]. This includes both care at home and public care homes. The mean life expectancy in Odense Municipality is 81.2 years (2018–2022) [24]. In 2021, 5500 citizens received home care [25]. The municipal home care is extensive and covers housing for older citizens, cleaning, personal care, help taking medication, physical training, provision of aids and appliances and help carrying out activities of daily living. The municipal home care works 24/7 and delivers care at home based on a needs assessment. The municipality also provides 1123 care home dwellings (i.e. “1123 dwellings” in care homes), not including dwellings in private care homes (*n* = 449). Furthermore, home care service is allocated to the individual citizen based on a needs assessment, and irrespective of the presence of a cohabitating partner. If a family member provides care for a relative, they can apply for respite or relief [26].

The municipality employs social and health care workers as well as nurses (community nurses; home-based-care nurses) to provide care and nursing care. All citizens are allocated a primary care physician, who serves as the gatekeeper to the hospital. The Danish health care system offers a universal health care coverage financed through taxes [27].

Odense University Hospital is a medium-sized university hospital situated in Odense municipality. It has 965 beds, 95,000 annual discharges and approximately 315,000 patient-days of admissions per annum. The hospital provides 412 of 652 highly specialised functions and approximately 10,000 employees [28]. Odense University Hospital primarily covers the island of Funen, Denmark, but has also many highly specialised functions offered both as regional functions and at a national level. It is the largest hospital in the Region of Southern Denmark and the second largest hospital in Denmark by number of beds.

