In terms of weaknesses, there will be a selection bias towards cognitively intact or mildly cognitively impaired patients with, at most, a diagnosis of mild dementia, as patients with moderate to severe dementia will be excluded due to the current research-ethical constraints regarding the inclusion of incapacitated patients. Yet, we believe that patients with moderate to severe dementia would benefit from the intervention, too. There may also be a performance bias, as participants in the intervention group may withhold contact to primary care physician if they feel worse after discharge as they know they will receive a follow-up visit shortly. The same performance bias is expected among the home care staff who visits the participants. This type of bias may lead to lower readmissions on its own.

Finally, the intervention is multifactorial encompassing multiple elements: (a) a home visit soon after discharge that may reassure both the participant, the relatives and the home care so that contact to the primary care physician is prevented, (b) a systematic approach securing that all potential bodily functions are assessed, (c) the use of vital status assessment and POCT analyses and (d) video contact to a geriatrician from the discharging department. We will thus not be able to disentangle, which of the elements has the greatest effect in the intervention, but as geriatric patients are complex, all elements of the interventions may add valuable information that supports clinical decision-making and relevant care to the patient.

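### The plan presumes no adverse effects and uses this to support a per-protocol-only claim of benefit, although its Discussion expects withheld primary care contact that could itself lower readmissions

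*Protocol article*

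**What the plan says.** **The premise and its use.** The protocol article (Statistical analyses) plans an ITT analysis with a complementary per-protocol analysis, and adds: "Given the negligible planning costs and absence of adverse effects, the intervention may still be considered clinically relevant". The sentence goes on to say when this applies: "even if statistical significance is only observed in the per-protocol population".

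**The behaviour the protocol expects.** Among the weaknesses in the Discussion, it says that "participants in the intervention group may withhold contact to primary care physician if they feel worse after discharge", because they know a visit is coming. It adds: "The same performance bias is expected among the home care staff who visits the participants". On the consequence it says: "This type of bias may lead to lower readmissions on its own". Setting and study population explains why contact with that physician matters for the endpoint: "All citizens are allocated a primary care physician, who serves as the gatekeeper to the hospital".

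**The endpoint and the safety measures.** "The primary outcome is 30-day acute readmission", compared by relative risk. The plan also has a 30-day mortality relative risk, 1-year mortality, days alive out of hospital at 30 and 90 days, a Cox and Kaplan-Meier analysis of time to readmission, and a statement that the competing risk of death will be considered. At the interim, "The outcomes examined in the interim analysis will be 30-day mortality and 30-day readmission rate", and a significant mortality difference is a stopping criterion.

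**The concern.** A trial should find out whether an intervention is free of adverse effects. Here that is assumed, and the assumption is used when the ITT result is not significant but the per-protocol result is. That is when caution is most needed, because the per-protocol comparison no longer has the protection of randomisation.

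The assumption also fits poorly with the rest of the article. The Discussion expects people who feel worse to delay seeking help because of their allocation. It lists late contact with the primary care physician among the problems of care transitions. The interim rule treats a mortality difference as possible.

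At stake is the interpretation. A lower readmission proportion could arise partly from withheld contact and still be reported as a clinically relevant benefit without harm.

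**Working it through.** **1. The plan's own figure.** Inputs from Sample power and statistical power: 19% against 19% × (1 − 0.28) = 13.68%, α = 0.05 (two-sided assumed), power 80%, 1:1.

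- Pooled variance: (1.960·√(2·0.1634·0.8366) + 0.842·√(0.19·0.81 + 0.1368·0.8632))² / 0.0532² gives 758 per arm.
- Unpooled variance gives 755.
- The stated 763 is within about 1% of both, and power at 763 per arm is 80.3%. The planned difference is 5.32 points.

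**2. How the readmission relative risk scores each course after withheld contact.**

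- Deteriorates, is admitted late but by day 30: counted as an event. Nothing is masked.
- Recovers without admission: not an event, and rightly so.
- Dies by day 30 without admission: not an event, so scored the same as a recovery. This death does appear in 30-day mortality and in days alive out of hospital.

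Only the third course turns a worse outcome into an apparent gain on the primary measure.

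**3. Size, as scenarios.** The documents give no rate of unadmitted death. Assume that x points of intervention participants who would have been readmitted die unadmitted instead, and that there is no other effect.

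| x (points) | Participants per 763 | Readmission RR | Share of 5.32 points |
|---|---|---|---|
| 0.5 | about 4 | 0.185/0.19 = 0.97 | 9% |
| 1 | about 8 | 0.18/0.19 = 0.95 | 19% |
| 2 | about 15 | 0.17/0.19 = 0.89 | 38% |

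**4. Why death-or-readmission helps.** Let d be the control proportion dying unadmitted. The composite is 19% + d in controls and (19% − x) + (d + x) = 19% + d in the intervention arm. The composite relative risk stays at 1, so the spurious gain disappears.

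**5. Why mortality alone is a limited safeguard.** Control 30-day mortality is not in the documents, so 3%, 5% and 8% are assumed. Power at 763 per arm is Φ(|difference|/SE − 1.96). For 5% against 7.5%, SE = √((0.05·0.95 + 0.075·0.925)/763) = 0.0124, and Φ(2.02 − 1.96) = 52%.

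| Control mortality | Power, RR 1.25 | Power, RR 1.5 | RR detectable with 80% power |
|---|---|---|---|
| 3% | 13% | 34% | 1.99 |
| 5% | 18% | 52% | 1.73 |
| 8% | 28% | 74% | 1.55 |

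A non-significant mortality comparison would therefore not establish an absence of adverse effects.

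**6. Withheld contact as the only effect.** Suppose there is no true benefit, and withheld contact alone removes a share f of intervention-arm readmissions, whatever then happens to those participants. For f = 10% the difference is 0.019 and SE = √((0.1539 + 0.1418)/763) = 0.0197, so the chance of a significant result favouring the intervention is Φ(0.965 − 1.960) = 16%. For f = 5%, 20% and 28% it is 7%, 51% and 80%. The documents give the direction of this effect but no value for f.

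**The case against.** The strongest reply is that the disputed phrase has a narrow role and that safety is examined. Much of this stands.

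- **The phrase serves only the per-protocol fallback.** Correct. It does not govern the ITT analysis. A reader might infer that the trial's whole conclusion rests on assumed harmlessness, but the sentence does not say so.
- **Safety is tested.** Also correct. It would be wrong to infer that harm goes unmeasured, given the planned mortality outcomes, days alive out of hospital and interim mortality check. What is missing is any link from these results to the claim of benefit.
- **The protocol describes a performance bias, not a harm.** True. That delayed help-seeking may injure participants is an inference. Routes through the on-call doctor, emergency services and round-the-clock home care remain. The inference is fair for people who feel worse, but the two sections are in tension and do not flatly contradict each other.
- **Delay is not masking.** Largely right. The visit follows soon after discharge and can itself lead to acute readmission, and a late admission within 30 days still counts.
- **Early events.** A reader might point to how many readmissions fall before the visit. With the article's median of nine days and an assumed truncated-exponential time to readmission over 30 days, 14% occur by day 2 and 41% by day 7. These are background events, and their share says nothing about harm from waiting.
- **Per-protocol exclusions.** A reader might also infer that people who die or are readmitted before the visit leave only the intervention arm. The article does not define the per-protocol set, so this cannot be asserted.

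**Conclusion.** The point holds in a limited form. The plan treats an untested safety conclusion as known and uses it to support a claim of benefit resting on per-protocol significance alone. This sits badly with the Discussion's account of withheld contact and with the plan's own mortality stopping criterion. The readmission relative risk cannot distinguish an unadmitted death from a recovery, and none of the planned safety results conditions the claim.

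The size is unknown. The relative risks of 0.97 to 0.89 and the 7% to 80% chances of a significant result are arithmetic on assumed inputs, not estimates. The mortality power figures rest on assumed control rates of 3% to 8%. The documents do not support saying that the intervention is harmful, that safety is untested, or that the primary ITT analysis is invalid. The fault lies in a rule of interpretation and can be corrected in the text.

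**What to change.** 1. Delete the absence of adverse effects as a premise in Statistical analyses.
2. State that the conclusion on benefit rests on the ITT result, and that per-protocol significance alone does not support such a claim.
3. Prespecify ITT 30-day death-or-readmission as a supportive analysis beside the readmission relative risk. Read it together with the planned 30-day mortality and days alive out of hospital, each with a confidence interval. Do not make it a veto on point estimates: with no true mortality effect, the estimate would fall on the wrong side about half the time by chance.
4. Optionally, tabulate deaths without prior readmission by arm in the final analysis.

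The changes apply to the final analysis, since the interim was set for January 2024 and the protocol version is dated April 2024. They should be recorded before the masked group labels are revealed.

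The cost is a change of wording and one extra analysis, from death and readmission data already collected for one year on every participant. The sponsor gives up the per-protocol-only fallback claim. Sample size and trial conduct are unaffected.
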